### Allocation

Participants will be randomized in a 1:1 parallel group design to each intervention arm through a computerized randomization sequence. Randomization is stratified by age (≤ 24, 25 +) and sex, as there is evidence that these variables can impact sleep and/or intervention outcomes [114, 115]. The planned stratified randomization is part of the generation of the randomization sequence. Randomization will be conducted by one project coordinator (i.e., UCB research staff). The assessors will be blind to the intervention arm of the participants.

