## Planned analyses

### Preliminary analyses and missing data

Data will be audited for quality and completeness. Missing or aberrant data will be verified for maximal data integrity. We will evaluate the distributions of the outcome variables and ensure that all the assumptions of planned analyses (e.g., linearity, normally distributed residuals) are met.

As per the power analysis described, we plan to recruit 160 participants, which allows for 20% attrition. Intent-to-treat analyses will use all available data via maximum likelihood estimation and produce valid inferences if attrition depends on intervention group or on previous outcomes for the same participant [118]. Additionally, sensitivity analyses may be conducted using multiple imputation to address missing data (e.g., dropouts, every item is not completed). If dropout is related to other variables, they will be included as predictors in the model to reduce any bias due to non-random missing data.

For Aims 1–3, all models will control for stratification factors (i.e., sex, age) used during the randomization procedure. Prior to the main analyses, appropriate statistical tests will be used to examine pre-treatment (i.e., baseline) differences between groups (e.g., education, current living arrangement, relationship status) to ensure comparability of the two randomized conditions (HABITs vs. HABITs + Texts) at pre-treatment and adequacy of the randomization. These tests will not be used to select covariates in the intent-to-treat analysis [119]. Instead, the potential influences of pre-treatment differences will be evaluated as moderators (described below in Exploratory Aim 1).

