### Aims 1–3: Effectiveness outcomes of HABITs versus HABITs + Texts

For Aims 1–3, we will use intent-to-treat analyses, including all randomized participants as randomized in the analysis regardless of their adherence or completion of the assigned intervention. We will use multilevel modeling [120] to account for multiple observations over time (pre-treatment, post-treatment, 6-month, and 12-month follow-up) nested within participants. The level 1 equation captures within-person variation across time and will include dummy-coded time indicators (0 = pre-treatment, 1 = post-treatment, 2 = 6-month follow-up, 3 = 12-month follow-up) as predictors. The level 2 equation captures between-person variations in the intercept and slope of time and will include dummy-coded intervention condition (0 = HABITs, 1 = HABITs + Texts) and intervention-by-time interaction terms, as predictors. The parameters of interest will be significant intervention-by-time interactions at the 5% level (i.e., differences in intervention effects on change in outcomes from pre-treatment to post-treatment, pre-treatment to 6-month follow-up, and pre-treatment to 12-month follow-up). Significant intervention-by-time interactions indicate that the trajectory of change on outcomes is significantly different over time, comparing HABITs + Texts to HABITs. For Aim 1a, utilization of sleep health behaviors, as indexed by the Utilization Scale will be modeled as the continuous outcome variable. For Aim 1b, sleep health behavior habits, as indexed by the primary measure (SRBAI-US), secondary measure (Adapted SRHI – Primary), and other measure (Adapted SRHI – Secondary), will be modeled as the continuous outcome variables, separately. For Aim 2, sleep and circadian functioning, as indexed by primary measures (i.e., CSHS, CSM, PROMIS-SRI, and PROMIS-SD) and secondary measures (i.e., PSQI, Sleep Diary and Actigraphy [night-to-night variability in the mid-point of sleep]) will be modeled as the continuous outcome variables, separately. For Aim 3, the latent variables of health risk, as indexed by the primary measure (Adapted WSAS) and secondary measures (i.e., DASS, PROMIS-CF, BSSS, PROMIS-APS, PHQ, and EMA Composite Risk Score^8^), will be modeled as the continuous outcome variables, separately.

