### Exploratory aim 1: mediators and moderators of intervention effects

Structural equation modeling [121] will be used to test whether sleep health behavior habit formation, as indexed by the SRBAI-US, mediate the effects of the intervention (HABITs vs. HABITs + Texts) on improving sleep and circadian functioning and health-relevant risk, as indexed by the primary measures for each. Bootstrapping procedure with 5000 replications will be used to test the statistical significance of the indirect effect from intervention condition to outcomes via the mediator [122]. The Benjamini–Hochberg procedure [123] will be used to correct for multiple testing on the outcomes (i.e., sleep and circadian functioning and health-relevant risk) [124]. Moderators will be assessed using a three-way interaction, intervention-by-time-by-moderator, in the multilevel model described in Aims 1–3. Each moderator and outcome will be tested in a separate model. Moderators will include age group (older adolescents 18–20 years of age vs. emerging adults 21–30 years of age), sex (sex assigned at birth; male, female, prefer not to say), and socioeconomic status (income; in 10,000 increment buckets [e.g., 0–10,000]).

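### Sex and age, read naturally as additive controls, do almost nothing for the intervention-by-time contrasts tested in Aims 1–3; crossing them with time would cost little

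*Protocol article*

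**What the plan says.** Four places in the Protocol article bear on this.

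- **Allocation:** "Randomization is stratified by age (≤ 24, 25 +) and sex, as there is evidence that these variables can impact sleep and/or intervention outcomes".
- **Preliminary analyses and missing data:** for Aims 1–3, "all models will control for stratification factors (i.e., sex, age) used during the randomization procedure". The same section sets the estimation method: "Intent-to-treat analyses will use all available data via maximum likelihood estimation". It plans for 20% attrition.
- **Aims 1–3 (effectiveness outcomes):** level 1 carries dummy-coded time. For level 2, "The level 2 equation captures between-person variations in the intercept and slope of time and will include dummy-coded intervention condition", together with "and intervention-by-time interaction terms, as predictors". The tests are then fixed: "The parameters of interest will be significant intervention-by-time interactions at the 5% level", that is, arm differences in change from pre-treatment to post-treatment, 6 months and 12 months.
- **Exploratory aim 1:** "Moderators will be assessed using a three-way interaction, intervention-by-time-by-moderator, in the multilevel model described in Aims 1–3". Here sex and age are crossed with time, but age is cut at 18–20 versus 21–30, not at the randomisation cut.

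Exploratory aim 2 repeats the promise to control for sex and age, in a model whose tested parameter is the plain coefficient of time.

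**The concern.** Sex and age group do not change within a participant over the trial. A term that is constant over time raises or lowers all four visits of a person by the same amount and drops out of every difference from pre-treatment. The tested parameters are exactly such differences. An additive control for the stratification factors would therefore leave them essentially unadjusted.

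The trial stratified because these factors may affect intervention outcomes, which can include change. If they do, stratified allocation balances that part of the variance between arms, while the test still counts it in its standard error. The standard error is then larger than the true sampling variability of the estimate. The test rejects less often than its nominal level and some power is lost.

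**Working it through.** **1. Form of the adjustment.** The article does not state it outright. Three features point to additive terms: the main model names intervention-by-time as its only time interaction; sex and age are crossed with time only in the exploratory moderator models; and Exploratory aim 2 uses the same control wording with a plain coefficient of time as its target. If the factors were crossed with time there without centring, that coefficient would describe the reference stratum only.

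**2. Cancellation.** Write the mean of participant i at visit t as

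μ(i,t) = α + τ(t) + β·arm(i) + γ(t)·arm(i) + δ₁·sex(i) + δ₂·age(i), with τ(0) = γ(0) = 0.

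Then μ(i,t) − μ(i,0) = τ(t) + γ(t)·arm(i). The terms δ₁ and δ₂ have gone. With sex-by-time and age-by-time terms they would remain, as δ₁(t)·sex(i) + δ₂(t)·age(i).

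**3. Numerical check.** Generalised least squares was run on simulated data with N = 160, four visits and arms balanced 1:1 within strata. The table gives the arm-by-time estimates under compound symmetry (correlation 0.5).

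| Data | Sex and age enter as | Post | 6 months | 12 months |
|---|---|---|---|---|
| Complete | not at all | 0.37212 | 0.43338 | 0.26811 |
| Complete | main effects | 0.37212 | 0.43338 | 0.26811 |
| Complete | main effects and by time | 0.37703 | 0.43776 | 0.26975 |
| About 20% missing | not at all | 0.6663 | 0.5186 | 0.3707 |
| About 20% missing | main effects | 0.6836 | 0.5285 | 0.3788 |

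With complete data the standard error is 0.15813 for each contrast, both without covariates and with main effects. Estimates and standard errors were also identical between those two forms under an arbitrary unstructured covariance. With missing visits, main effects move the estimates by 0.0173, 0.0099 and 0.0081, against standard errors of about 0.17. This check holds the covariance fixed, so it shows which terms act on the contrasts but not the gain in precision. Step 4 gives that.

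**4. Consequence for size and power.** Let R² be the share of the variance in change explained by sex and age group. The article does not give it, so a range is assumed. Take k = √(1 − R²), z = 1.960 (two-sided 5%) and ncp = 2.802, which gives 80% power at R² = 0. The 80% is the article's target. At 5% it corresponds to 64 per arm with d = 0.50, where t-test power is 0.801; this point does not depend on the sample-size figures.

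- Size without the time terms: 2·[1 − Φ(z/k)].
- Power without them: Φ((ncp − z)/k). Stratification has already reduced the true variability, so this is not fixed at 80%.
- Power with them: Φ(ncp/k − z).

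| R² | Size without | Power without | Power with | Gain (points) |
|---|---|---|---|---|
| 2% | 4.8% | 80.2% | 80.8% | 0.5 |
| 5% | 4.4% | 80.6% | 82.0% | 1.4 |
| 9% | 4.0% | 81.1% | 83.6% | 2.5 |
| 13% | 3.6% | 81.7% | 85.2% | 3.5 |

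Example at R² = 5%: k = 0.9747 and z/k = 2.011, so size = 4.4%. Power is Φ(0.8416/0.9747) = 80.6% without the terms and Φ(2.874 − 1.960) = 82.0% with them.

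**5. Simulation.** In 8,000 stratified trials with n = 128, R² of 2%, 5% and 10% gave size without the time terms of 4.8%, 4.2% and 3.8%. Power was 80.7% against 81.4%, 80.7% against 82.1%, and 81.7% against 84.6%. This agrees with step 4 within simulation error.

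**The case against.** The strongest reply is that additive entry is inferred. The article says only that the models control for sex and age. Level 2 is described as covering both the intercept and the slope of time, so crossing the factors with time is compatible with the text. The predictor list for the main model omits even the sex and age main effects, so it is not a complete specification. A condensed article may leave this detail to the analysis plan. All of that stands, which is why the point is a request for a sentence and not a claim of error. The additive reading is still the natural one, for the reasons in step 1.

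A reader might infer more than the documents support:

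- **That the control cannot adjust the contrasts at all.** This is true only with complete data. Under maximum likelihood with missing visits, main effects do move the estimates, though slightly.
- **That the tests ignore the stratification.** They do not. Stratification still balances the arms and lowers the true variance of the estimates; what is missing is credit for it in the standard error.
- **That dropout imbalance within strata goes uncorrected for this reason.** Sex and age terms of any form cannot address imbalance within strata. The article separately plans to add predictors of dropout to the model.
- **That the power loss is larger.** Holding the unadjusted test at 80% power for every R² gives larger gains, but it overlooks that stratification raises that test's power as well.

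**Conclusion.** The point holds as a small improvement. As naturally read, the stated control for the stratification factors does almost nothing for the parameters of interest. The tests remain valid and unbiased and the type I error is not inflated; the only cost is conservatism and a little power. With an assumed R² of 2% to 13%, size at a nominal 5% is about 4.8% to 3.6% and the power forgone is about 0.5 to 3.5 points. At R² = 5% it is 1.4 points, and at R² = 0 it is nothing.

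The conclusion rests on the additive reading and on an R² that the article does not report. If the analysis plan already crosses both factors with time, the point falls away.

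**What to change.** In Preliminary analyses and missing data, and in the Aims 1–3 model description, state that sex and age group as randomised (≤ 24, 25+) enter every Aims 1–3 model both as main effects and crossed with the time indicators. State also that the intervention-by-time terms remain the tested parameters.

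With two-level factors the cost is 2 × 3 = 6 extra fixed effects in a four-visit model and 2 × 1 = 2 where only pre- and post-treatment data exist (actigraphy and EMA). The loss of degrees of freedom is negligible with 128 to 160 participants. Design, sample size and data collection do not change. Data collection is planned to July 2026, so the wording can be settled before the final analysis.

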### Dropout

Per CONSORT figure recommendations [119], the *N* by stage of dropout will be reported for the following: dropout after randomization, dropout after treatment has been completed but prior to post-treatment, 6-month, or 12-month follow-up assessments.a

### Aims 1–3: Effectiveness outcomes of HABITs versus HABITs + Texts

For Aims 1–3, we will use intent-to-treat analyses, including all randomized participants as randomized in the analysis regardless of their adherence or completion of the assigned intervention. We will use multilevel modeling [120] to account for multiple observations over time (pre-treatment, post-treatment, 6-month, and 12-month follow-up) nested within participants. The level 1 equation captures within-person variation across time and will include dummy-coded time indicators (0 = pre-treatment, 1 = post-treatment, 2 = 6-month follow-up, 3 = 12-month follow-up) as predictors. The level 2 equation captures between-person variations in the intercept and slope of time and will include dummy-coded intervention condition (0 = HABITs, 1 = HABITs + Texts) and intervention-by-time interaction terms, as predictors. The parameters of interest will be significant intervention-by-time interactions at the 5% level (i.e., differences in intervention effects on change in outcomes from pre-treatment to post-treatment, pre-treatment to 6-month follow-up, and pre-treatment to 12-month follow-up). Significant intervention-by-time interactions indicate that the trajectory of change on outcomes is significantly different over time, comparing HABITs + Texts to HABITs. For Aim 1a, utilization of sleep health behaviors, as indexed by the Utilization Scale will be modeled as the continuous outcome variable. For Aim 1b, sleep health behavior habits, as indexed by the primary measure (SRBAI-US), secondary measure (Adapted SRHI – Primary), and other measure (Adapted SRHI – Secondary), will be modeled as the continuous outcome variables, separately. For Aim 2, sleep and circadian functioning, as indexed by primary measures (i.e., CSHS, CSM, PROMIS-SRI, and PROMIS-SD) and secondary measures (i.e., PSQI, Sleep Diary and Actigraphy [night-to-night variability in the mid-point of sleep]) will be modeled as the continuous outcome variables, separately. For Aim 3, the latent variables of health risk, as indexed by the primary measure (Adapted WSAS) and secondary measures (i.e., DASS, PROMIS-CF, BSSS, PROMIS-APS, PHQ, and EMA Composite Risk Score^8^), will be modeled as the continuous outcome variables, separately.

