## Aims

This randomized controlled two-arm parallel group superiority study with 1:1 allocation ratio will be conducted with young adults who are 18–30 years of age, exhibit an eveningness chronotype, and demonstrate elevated symptoms in one of the five health domains. Participants will be randomized (1:1) to HABITs alone or HABITs plus Text Message Intervention (HABITs + Texts). There are three aims.

Aim 1 is to assess if adding a text message intervention to HABITs improves sleep health behaviors in the short (post-treatment) and longer term (6-month and 12-month follow-up), relative to HABITs alone. Hypothesis 1 is that, relative to HABITs, participants in HABITs + Texts will (a) report utilizing more sleep health behaviors and (b) establish stronger sleep health behavior habits. We hypothesize that these effects (1a and 1b) will be observed from pre-treatment to post-treatment, pre-treatment to 6-month follow-up, and pre-treatment to 12-month follow-up.

Aim 2 is to assess if adding a text message intervention to HABITs improves sleep and circadian functioning in the short (post-treatment) and longer term (6-month and 12-month follow-up), relative to HABITs alone. Hypothesis 2 is that, relative to HABITs, participants in HABITs + Texts will exhibit improved sleep and circadian functioning. We hypothesize that this effect will be observed from pre-treatment to post-treatment, pre-treatment to 6-month follow-up, and pre-treatment to 12-month follow-up.

Aim 3 is to assess if adding a text message intervention to HABITs improves functioning in the five health-relevant domains in the short (post-treatment) and longer term (6-month and 12-month follow-up), relative to HABITs alone. Hypothesis 3 is that, relative to HABITs, participants in HABITs + Texts will exhibit lower health risk. We hypothesize that this effect will be observed from pre-treatment to post-treatment, pre-treatment to 6-month follow-up, and pre-treatment to 12-month follow-up.

As an Exploratory Aim 1, comparing HABITs and HABITs + Texts, we will examine (a) if the strength of sleep health behavior habit formation mediates the effects of the intervention (specifically by adding the text intervention to HABITs) on improvement in sleep and circadian outcomes, and health-relevant domain outcomes, and (b) if intervention effects are moderated by selected variables (i.e., age, sex, and socioeconomic status).

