##### Sleep diary and actigraphy

The Sleep Diary and Actigraphy will be used to calculate night-to-night variability in the mid-point of sleep for the Composite Sleep Health Score. The Sleep Diary is a self-report adapted version of the consensus sleep diary [90], to track subjective sleep for 7 days. The sleep diary will be collected at all assessments and at each session during treatment. The Actigraphy (Actiwatch® GT9X Link; Philips Respironics) will assess movement samples in 60-s epochs over a 7-day period. Actigraphy will only be collected at the pre-treatment and post-treatment assessments. The intra-individual variability will be calculated using the estimated within-subject standard deviation [91].

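### The Aims 1–3 model leaves the arm difference at pre-treatment free, which is valid but gives up precision, and its person-level slope of time does not fit dummy-coded visits

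*Protocol article*

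**What the plan says.** The section on Aims 1–3 under Planned analyses puts four occasions into a multilevel model, using "dummy-coded time indicators (0 = pre-treatment, 1 = post-treatment, 2 = 6-month follow-up, 3 = 12-month follow-up) as predictors". Pre-treatment is thus one of the outcome rows. On the person level: "The level 2 equation captures between-person variations in the intercept and slope of time and will include dummy-coded intervention condition", together with the intervention-by-time terms. The test is then fixed: "The parameters of interest will be significant intervention-by-time interactions at the 5% level", and these are explained as "differences in intervention effects on change in outcomes from pre-treatment to post-treatment" and likewise to 6 and 12 months. The hypotheses in the Aims section have the same form; the effects "will be observed from pre-treatment to post-treatment, pre-treatment to 6-month follow-up, and pre-treatment to 12-month follow-up".

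The section on preliminary analyses and missing data adds that "all models will control for stratification factors (i.e., sex, age) used during the randomization procedure" and that "Intent-to-treat analyses will use all available data via maximum likelihood estimation". It does not name the pre-treatment value of the outcome as a covariate.

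Three facts elsewhere matter. The Procedure section places consent and the pre-treatment assessment before enrolment and random allocation. Some outcomes assigned to this model have only two occasions: "Actigraphy will only be collected at the pre-treatment and post-treatment assessments", and Table 4 shows the same for the EMA composite. The Adapted SRHI measures have no pre-treatment value at all (Table 4 and the descriptions of both scales).

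**The concern.** An intervention main effect beside interactions that take pre-treatment as reference is, by construction, the arm difference at pre-treatment. Participants are allocated only after that assessment, so its expected value is zero. Estimating it brings its sampling error into every contrast that starts from pre-treatment. Neither a constraint nor a baseline covariate removes that error. The stake is power on the primary contrasts, lost although the baseline values are collected anyway.

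The second matter is the random part. With time entered as three dummies there is no single slope of time to vary between persons. The analyst must decide what was meant, and at least one natural reading has more covariance parameters than the data can determine.

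**Working it through.** **Inputs.** From the Sample size section: d = 0.60, two-sided alpha 0.017 per aim, 128 evaluable participants (64 per arm at 1:1), 80% power, 20% attrition. From the Aims 1–3 section: a 5% test level. Assumed, because the article gives none: the correlation rho between the pre-treatment value and the value at a later visit, and equal variances across visits. The d is read in units of the SD at one visit.

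**The plan's own figure.** 128/(1 − 0.20) = 160 is right. The 128 is not reproduced by d = 0.60 with alpha 0.017, which needs 116 (normal) or 120 (t); d = 0.50 with two-sided alpha 0.05 gives 126 or 128. That mismatch, and the 5% against 0.017, are separate matters. Here I keep 64 per arm and the stated d and alpha.

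**Variance of the two contrasts**, complete data, in units of the visit variance:

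- difference in change (free baseline): 2(1 − rho)
- common baseline mean, or baseline as covariate: 1 − rho²
- ratio: (1 − rho²)/[2(1 − rho)] = (1 + rho)/2

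**Power**, normal approximation, critical value 2.387 for alpha 0.017. Worked for rho = 0.3:

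- difference in change: SD = √1.4 = 1.183; 0.60/1.183 × √(64/2) = 2.869; Φ(2.869 − 2.387) = 0.685
- common baseline: SD = √0.91 = 0.954; 0.60/0.954 × √(64/2) = 3.558; Φ(3.558 − 2.387) = 0.879

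| rho | 2(1−rho) | 1−rho² | variance saved | power at 0.017 | power at 0.05 |
|---|---|---|---|---|---|
| 0.3 | 1.40 | 0.91 | 35% | 0.685 → 0.879 | 0.818 → 0.945 |
| 0.5 | 1.00 | 0.75 | 25% | 0.843 → 0.937 | 0.924 → 0.975 |
| 0.7 | 0.60 | 0.51 | 15% | 0.977 → 0.991 | 0.992 → 0.997 |
| 0.8 | 0.40 | 0.36 | 10% | 0.999 → 0.999 | no gain left |
| 0.9 | 0.20 | 0.19 | 5% | no gain left | no gain left |

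At rho = 0.5 the factor 2(1 − rho) is 1, so the planned test has exactly the power of the two-sample calculation. It has less below 0.5 and more above.

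**With dropout.** Generalised least squares with 80 per arm, 20% monotone dropout by 12 months and equal correlation between all visits (all assumed) gives 12-month variances of 0.0404 → 0.0281, 0.0292 → 0.0229 and 0.0177 → 0.0154 for rho = 0.3, 0.5 and 0.7. The savings are 30%, 21% and 13%.

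**Identifiability.** With q correlated random effects and a residual there are q(q+1)/2 + 1 covariance parameters; T visits supply T(T+1)/2 elements.

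- four visits, intercept and three correlated dummy slopes: 4·5/2 + 1 = 11 for 10 elements (rank 10): not identified
- four visits, intercept and one slope on 0–3: 2·3/2 + 1 = 4 for 10 (rank 4): identified
- four visits, uncorrelated random dummies: 4 + 1 = 5 (rank 5): identified
- two visits (actigraphy, EMA), intercept and correlated slope: 4 for 3 (rank 3): not identified

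In the two cases that are not identified, the marginal covariance matrix is still determined, so the fixed interaction terms can be estimated.

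**The case against.** The best defence is that nothing here is wrong in the strict sense. The hypotheses are stated as change from pre-treatment, the interactions test exactly that, and under randomisation the estimate is unbiased. That stands: the first half of the point is about efficiency, not validity. It does not dispose of it, because a model with a common baseline mean estimates the same difference in change with smaller variance.

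A second defence is that a condensed article may leave the covariance structure to the analysis plan. That is fair as to detail. But this text does state a random slope beside dummy-coded time, and the two do not fit together.

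A reader might infer more than the article supports:

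- *That the whole model cannot be identified or will not converge.* The wording is a single slope, and one slope on 0–3 is identified with four visits. All primary measures have four visits. That reading does, however, sit badly with dummy coding and treats unequal intervals as equal.
- *That every test is affected.* The Adapted SRHI has no pre-treatment value, and under dropout the maximum likelihood contrast is no longer the raw difference in change.
- *That the analyst would fall back on a random intercept and so inflate the type I error.* The article mentions no such fallback.
- *That this leaves the trial short of its stated power.* On the article's own d and alpha the planned test has power 0.843 at rho = 0.5 and 0.977 at 0.7. It falls below 80% only at lower correlations (0.762 at rho = 0.4), and no correlation is documented.

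**Conclusion.** For outcomes measured at pre-treatment, the planned contrast is valid but gives up precision that costs nothing to recover. The gain rests on an undocumented correlation: material at rho of 0.3 to 0.5, where it is worth 54% to 33% more participants (1/0.65 and 1/0.75), modest at 0.7, and negligible at 0.8 or above. These figures assume complete data and equal variances; the dropout calculation lowers the saving somewhat without changing the picture.

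The random part is a specification problem, not a source of invalid inference. Three correlated dummy slopes fail for four visits, and a correlated slope fails for the two-visit outcomes. The text should name a structure that can be fitted to every outcome assigned to the model.

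**What to change.** State the following before analysis.

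1. For outcomes with a pre-treatment value: time as a factor, arm-by-time terms for the later visits only, and no arm main effect at pre-treatment, so that both arms share one baseline mean. Alternatively, model the later visits with the pre-treatment value as covariate, its coefficient allowed to differ by visit.
2. Sex and age stay as fixed effects, as planned.
3. Replace the random slope with an unstructured within-person covariance: 4×4 for four-visit outcomes and 2×2 for actigraphy and EMA.
4. For the Adapted SRHI measures, compare the arms at post-treatment, 6 months and 12 months, since no change from pre-treatment exists.

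The cost is wording in the analysis plan. No further data, visits or participants are needed, and the hypotheses keep their meaning. The common baseline mean relies only on allocation following the pre-treatment assessment, which the Procedure section describes.

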### Sample size

The sample size was determined by power analysis (via G*Power 3.1). Two-tailed alpha of 0.05 with a Bonferroni-corrected alpha of 0.017 for each of the three aims. The effect size was drawn from prior research on text message health interventions (*d* = 0.60) [64, 116, 117]. To achieve 80% power, 128 participants will be needed to detect between medium-effect-size group differences. We added 20% to account for attrition, yielding 160 participants.

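### The protocol gives two significance levels for Aims 1–3, 0.017 per aim and 5% per interaction, and no success rule across 21 primary tests

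*Protocol article*

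**What the plan says.** Two sections of the protocol article set a significance level for the same comparisons.

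- **Sample size:** "Two-tailed alpha of 0.05 with a Bonferroni-corrected alpha of 0.017 for each of the three aims". The section then gives d = 0.60 and continues: "To achieve 80% power, 128 participants will be needed to detect between medium-effect-size group differences".
- **Planned analyses, Aims 1–3:** "The parameters of interest will be significant intervention-by-time interactions at the 5% level". These parameters are spelled out as the between-arm differences in change from "pre-treatment to post-treatment, pre-treatment to 6-month follow-up, and pre-treatment to 12-month follow-up".

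Table 4 lists seven primary measures, and the Aims 1–3 section assigns them to aims and models each outcome on its own:

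- Aim 1: Utilization Scale and SRBAI-US
- Aim 2: CSHS, CSM, PROMIS-SRI and PROMIS-SD
- Aim 3: Adapted WSAS total

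No measure or time point is singled out as the confirmatory test of an aim. The only multiplicity procedure in the analysis sections is Benjamini–Hochberg, and it is attached to the mediation tests of Exploratory Aim 1.

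**The concern.** The two levels give different answers. An interaction with p = 0.03 on PROMIS-SD at 6 months fails at 0.017 and succeeds at 5%. Because the article fixes both figures, this is a contradiction within the document and not a detail left to an unseen analysis plan.

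The level also bears on what follows. According to the Aims and Exploratory aim 2 sections, the pooled analysis is run if the between-arm effects are non-significant. An unclear threshold therefore makes that trigger unclear.

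A second gap lies underneath. A level of 0.017 per aim controls an aim-level claim only if the aim rests on one test, or if the level is shared among its tests. Aim 2 has twelve primary contrasts and no sharing rule.

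**Working it through.** **Inputs.** From the Sample size section: two-tailed 0.05, 0.017 per aim, d = 0.60, 80% power, 128 evaluable, 20% attrition, 160 in total. From the Allocation section: 1:1. From the Aims 1–3 section and Table 4: 2, 4 and 1 primary measures, three contrasts each.

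**1. The plan's own figure.** Two-group comparison of means, n per arm ≈ 2(z₁₋α/₂ + z₀.₈)²/d², then solved exactly with the noncentral t:

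| d | two-sided α | N, normal approximation | N, t-test |
|---|---|---|---|
| 0.60 | 0.017 | 116 | 120 |
| 0.50 | 0.017 | 168 | 170 |
| 0.50 | 0.05 | 126 | **128** |
| 0.60 | 0.05 | 88 | 90 |

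The stated inputs (d = 0.60, α = 0.017) give 120, or 120/0.8 = 150 after attrition. The stated 128 is matched exactly by d = 0.50 at an uncorrected 0.05, and 128/0.8 = 160. A one-sided 0.017/3 = 0.00567 at d = 0.60 comes close (128 by normal approximation, 130 by t-test), but the section says two-tailed.

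**2. Number of primary tests.** (2 + 4 + 1) × 3 = 21, which is 6, 12 and 3 for Aims 1, 2 and 3.

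**3. Chance of at least one false positive if the tests are independent**, 1 − (1 − α)^k:

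- 5%, all 21 tests: 1 − 0.95²¹ = 65.9%
- 5%, by aim: 1 − 0.95⁶ = 26.5%; 1 − 0.95¹² = 46.0%; 1 − 0.95³ = 14.3%
- 0.017, all 21 tests: 1 − 0.983²¹ = 30.2%
- 0.017, one test per aim: 1 − 0.983³ = 5.0%, the overall control that the sample-size section implies

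**4. The same with correlation.** The tests are not independent: the measures come from the same people, and the three contrasts share the pre-treatment value. The protocol gives no correlations, so the following are assumptions. The model is a multivariate-normal simulation of the 21 test statistics under no effect, 200,000 draws, with one common correlation between measures and one between time contrasts.

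| Between measures | Between contrasts | All 21 at 5% | Aim 1 at 5% | Aim 2 at 5% | Aim 3 at 5% | All 21 at 0.017 | Aim 2 at 0.017 |
|---|---|---|---|---|---|---|---|
| 0.3 | 0.5 | 56.1% | 22.9% | 39.2% | 12.5% | 25.5% | 16.2% |
| 0.3 | 0.7 | 50.8% | 20.2% | 34.7% | 10.9% | 22.6% | 14.3% |
| 0.5 | 0.5 | 49.2% | 21.9% | 35.6% | 12.6% | 21.8% | 14.5% |
| 0.5 | 0.7 | 44.1% | 19.2% | 31.5% | 11.0% | 19.4% | 12.8% |
| 0.7 | 0.5 | 39.9% | 20.3% | 30.4% | 12.7% | 17.4% | 12.5% |
| 0.7 | 0.7 | 35.1% | 17.7% | 26.6% | 10.9% | 15.1% | 10.8% |

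**5. Reading.** In every row each aim is well above 1.7% when tested at 5%. Replacing 5% by 0.017 without a rule within the aim leaves Aim 2 at 11–16%.

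**The case against.** The strongest reply is that the 5% in the analysis section is loose shorthand for the overall level. The sample-size sentence itself names 0.05 and 0.017 together, and further multiplicity detail would normally sit in an analysis plan. The first part is possible. But the analysis section attaches 5% to the interactions themselves, and nothing carries 0.017 into it, so the text still needs reconciling.

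A second reply is that the sample-size section commits only to a split across three aims and says nothing about measures or time points. The hypotheses expect effects at all three times. If support required all three contrasts, no adjustment across time would be needed. This stands as a limit on the error figures: no passage says that one significant contrast is enough. Nor does any passage require all three. Even then, seven measures at 5% could give up to 1 − 0.95⁷ = 30.2% if independent, and the conflict between 5% and 0.017 would remain.

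Two stronger readings are tempting.

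- A reader might infer that the trial has a 66% chance of a false claim. That needs independent tests and an any-contrast success rule, and the documents support neither.
- A reader might infer that the sample size was calculated at 0.017 and the analysis then abandoned it. The arithmetic does not bear this out, because 128 is what an uncorrected 0.05 gives at d = 0.50. The documents show two conflicting statements; they do not show which was intended.

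**Conclusion.** The point holds as a contradiction between the Sample size and Aims 1–3 sections, together with a missing success rule per aim. The contradiction and the count of 21 come straight from the text and need no assumption.

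The error rates are conditional. They apply if any single significant contrast is read as support, and the ranges below 66% rest on assumed correlations. The Aim 2 range of 27–39% holds for between-measure correlations of 0.3–0.7; about 41% is reached only with zero correlation between measures. Over the whole assumed range the conclusion is the same: neither 5% nor a bare 0.017 per test delivers 1.7% per aim.

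This concerns the decision rule only. It does not affect the effect estimates or the conduct of the trial, and it can be settled before outcomes are analysed, since the Trial status section has data collection running to July 2026.

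**What to change.** In the Aims 1–3 section, replace the 5% level with a rule that holds each aim at 0.017. Either option would serve:

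1. Name one confirmatory measure and one time point per aim, tested at 0.017, with the other primary contrasts supportive. This is simplest, but Aim 1 has two hypotheses (1a and 1b) and one would lose confirmatory status.
2. For each primary measure, run one joint 3-df test of the intervention-by-time terms, with Holm at 0.017 across the measures of an aim (two for Aim 1, four for Aim 2, one for Aim 3). After a significant joint test, test the three time contrasts with a stated adjustment, for example Holm at that measure's level. If time-specific claims must also stay within 0.017 per aim, give each measure a fixed share for both steps: 0.017/2 = 0.0085 in Aim 1, 0.017/4 = 0.00425 in Aim 2 and 0.017 in Aim 3.

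Secondary and other measures can stay at 5%, labelled as not multiplicity-controlled. State that the Exploratory Aim 2 trigger uses the same rule.

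Reconcile the Sample size section at the same time: state which effect size and alpha produce 128, or correct the figure.

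The change is to wording in the analysis plan and registry, but it costs power per measure. For a single contrast in a two-group t-test with 64 per arm at 0.017, power is 83% at d = 0.60 and 66% at d = 0.50, against about 80% at d = 0.50 and 0.05. These figures do not carry over to the joint test, whose power depends on how the effect is spread over the three time points and should be worked out before option 2 is chosen.
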